**Fig. 1 Fig1:**
[figure not shown]
Design flowchart

### Participants, recruitment, and eligibility criteria

A sample of 174 healthcare workers will be recruited from the Spanish healthcare system (hospitals, primary care centers, and nurse care centers). Participants will be eligible if they meet the inclusion criteria: 1) being an active healthcare worker and 2) having an Android smartphone with Internet access. Participants will be excluded if they are already receiving a psychological treatment at the time of the recruitment or 2) having a smartphone with an operating system different to Android. Participants will be recruited from two sources: 1) volunteers from a large healthcare provider company (GESMED company, with 2.500 healthcare workers at the region) and 2) volunteers from different healthcare organizations recruited online using social media (paid campaigns) and personal contacts.

### Sample size

The sample size was calculated a priori using GPower [68]. Assuming a conservative effect size of 0.20, an alpha level of 0.05, an 80% power, three groups, and 3 measurements, a sample of 152 was obtained. Assuming a 15% of attrition, we will recruit a minimum of 174 participants. The small attrition rate is based on a systematic review showing that interventions for mental health that incorporate technology, such as blended interventions, tend to obtain lower dropout rates [69]. The effect size in favor of EMI compared to EMA and the control condition is also inspired by past research [70].

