**Methods:**

In this three-arm, randomized controlled trial (RCT) the study sample will be composed of a minimum of 174 healthcare workers. They will be randomly assigned to a 2-month EMI group (CUIDA-TE APP, *n* ≥ 58), a 2-month ecological momentary assessment (EMA) only group (MONITOR EMOCIONAL APP, n ≥ 58), or a wait-list control group (no daily monitoring nor intervention, n ≥ 58). CUIDA-TE will provide EMI if EMA reveals emotional problems, poor sleep quality/quantity, burnout, stress, or low perceived self-efficacy when regulating emotions. Depression will be the primary outcome. Secondary outcomes will include emotion regulation, quality of life, and resilience. Treatment acceptance and usability will also be measured. Primary and secondary outcomes will be obtained at pre- and post-intervention measurements, and at the 3-month follow-up for all groups.

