## Data analysis plan

First, to ensure that the randomization process was successful, the three study conditions will be compared at baseline on all study outcomes. Then, a multilevel linear mixed model, which effectively handles missing data, will be computed. All assessment points will be included in the model. A restricted maximum likelihood method will be used to estimate the parameters. If differences at baseline are revealed, we will include them as covariates in the linear mixed model. Effect sizes (Cohen’s d) will be calculated [103]. Usability and acceptability will be evaluated with descriptive analyses.

All analyzes will be performed with SPSS v26.0. To conduct and report the study, we will follow the recommendations of the Consolidated Standards of Reporting Trials (CONSORT) [67].

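### The 80% power at N = 152 belongs to an omnibus three-arm test. It is not established for EMI versus EMA or EMI versus wait-list, and 0.20 cannot be read as a small pairwise effect

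*Protocol article*

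**What the plan says.** The Sample size section of the protocol article states "The sample size was calculated a priori using GPower". Its inputs are "Assuming a conservative effect size of 0.20, an alpha level of 0.05, an 80% power, three groups, and 3 measurements", and the result is 152, raised to 174 for attrition. The metric of the 0.20 (d, f or f(V)), the G*Power test and the correlation between repeated measures are not given. The section then describes the assumption in pairwise terms: "The effect size in favor of EMI compared to EMA and the control condition is also inspired by past research".

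Study aims and design sets EMI against the EMA group and against the wait-list. The current study treatment adds that the EMA-only arm is there to separate the effect of assessment from that of the intervention. The only effect-size metric named anywhere is in the Data analysis plan: "Effect sizes (Cohen’s d) will be calculated". The Abstract gives at least 58 participants in each arm.

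**The concern.** A reader who sees a conservative 0.20 described as EMI's advantage over EMA and control, with Cohen's d as the only metric in the article, will conclude that the trial has 80% power to show a small pairwise difference. The listed inputs, "three groups, and 3 measurements", point instead to a test of any difference in change among the three arms.

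A significant omnibus test does not show that EMI beats EMA, and its power is not the power of that comparison. At stake is the reading of a null EMI versus EMA result: someone relying on the 80% would take it as evidence that the intervention adds nothing to daily monitoring. The protocol also makes the later offer of CUIDA-TE to EMA participants depend on the results.

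**Working it through.** **Inputs.** From the protocol: 0.20, alpha 0.05, power 80%, 3 groups, 3 measurements. Completers per arm: 152/3 = 50.7, or 174 × 0.85 / 3 = 49.3, so n = 50. Assumed, because not stated: correlation ρ between measurements of 0.5 to 0.7, equal for all pairs; an effect of the same size at post-treatment and follow-up; two-sided 0.05.

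**1. Reproducing 152.** MANOVA group-by-time interaction: λ = N × s × f(V)², with s = 2, df1 = 4, df2 = 2(N − 3).
- N = 151: power 0.798.
- N = 152: λ = 152 × 2 × 0.04 = 12.16, power 0.801. So 152 is the exact minimum.

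Other routes to about 152:
- Default repeated-measures interaction with f = 0.10 (which is d = 0.20 for two groups) and ρ = 0.625: λ = 152 × 3 × 0.01 / 0.375 = 12.16, again exactly 152.
- ANOVA interaction with the SPSS-type effect size: 152 or 155, depending on whether λ uses N or N − 3.
- Between-groups test with f = 0.20 and ρ = 0.42: 151.

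All are omnibus three-group tests. With f = 0.20, these do not match: default interaction at ρ = 0.5 (53), Cohen-type effect size (102), between-groups at ρ = 0.5 (164), one-way ANOVA (244).

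**2. If 0.20 is a pairwise d.** Required n per arm = 2(1.96 + 0.8416)² / 0.20² = 392.4, so 393. Baseline adjustment multiplies this by 1 − ρ²: 295 at ρ = 0.5, 201 at ρ = 0.7.

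Power with n = 50 uses the noncentral t with δ = (d/SD) × √(n/2) = 5d/SD:
- unadjusted, SD = 1: δ = 1.00, power 17%;
- baseline-adjusted, SD = √(1 − ρ²): 21% at ρ = 0.5, 28% at ρ = 0.7.

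**3. If f(V) = 0.20 is the true effect.** V = 2 × 0.04/1.04 = 0.0769. The corresponding root is 0.0769/(1 − 0.0769) = 0.0833.
- EMI differs and EMA equals wait-list: d = √(0.0833 × 27(1 − ρ)/4) = 0.53 at ρ = 0.5, 0.41 at ρ = 0.7.
- EMA midway: EMI versus wait-list d = √(0.0833 × 9(1 − ρ)) = 0.61 or 0.47. EMI versus EMA is half of that, 0.31 or 0.24.

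Power per contrast, n = 50:

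| Analysis | SD | EMI contrast, EMA equals wait-list | EMI versus EMA, EMA midway |
|---|---|---|---|
| Change score, one time point | √(2(1 − ρ)) | 75% | 33% |
| Baseline-adjusted, one time point | √(1 − ρ²) | 86% (ρ = 0.5) to 81% (ρ = 0.7) | 42% to 38% |
| Baseline-adjusted, mean of both post-baseline points | √((1 + ρ)/2 − ρ²) | not computed | 57% to 50% |

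Example, last row at ρ = 0.5: SD = √(0.75 − 0.25) = 0.707, δ = 5 × 0.306/0.707 = 2.16, power 57%.

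**4. Detectable pairwise difference, n = 50, 80% power, one time point.** Unadjusted: 0.57 SD. Baseline-adjusted: 0.566 × √(1 − ρ²) = 0.49 SD at ρ = 0.5 and 0.40 SD at ρ = 0.7.

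**The case against.** The 152 reproduces, so there is no arithmetic error. The article discloses three groups and three measurements, which an informed reader may take as a sign of a repeated-measures test. Cohen's d appears only as a reporting measure, and naming the G*Power option is detail that a condensed article can omit. These points stand, but they do not remove the sentence that ties the 0.20 to EMI against EMA and control.

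The metric is inferred. A reader might conclude that the sponsor used f(V), or that no route starting from d = 0.20 can give 152. The article supports neither: f = 0.10 with a correlation of 0.625 gives the same number.

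A reader might also infer that pairwise power falls short whatever the truth. It does not. If EMA does no better than wait-list, baseline-adjusted power is 81% to 86% per contrast, which fits a reading in which EMI alone stands out. Against this, the protocol describes daily assessment as a first step in emotion regulation that may itself help, and that makes an intermediate EMA effect plausible.

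The mixed model uses all assessments, and EMA participants are offered CUIDA-TE only after follow-up, so a single-time-point figure is pessimistic for EMI versus EMA. Using both points raises power to 50% to 57%, still well below 80%.

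Finally, whether 0.20 is conservative relative to the cited research cannot be judged from the article. The choice of contrasts, decisive time point and multiplicity procedure may properly sit in an analysis plan that is not shown. Neither is part of this point.

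**Conclusion.** The point holds as a misattributed power statement. The 80% was obtained for an omnibus three-group test on every route found, while the text attaches the effect size to pairwise superiority of EMI.

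The size of the problem depends on what 0.20 means and on the pattern of means. As a pairwise d of 0.20, power is 17% to 28%. At the omnibus effect, power per EMI contrast is about 75% to 86% if EMA equals wait-list, but 33% to 42% (50% to 57% using both post-baseline points) for EMI versus EMA if EMA is midway. These figures rest on 50 completers per arm, two-sided 0.05 without a split across comparisons, assumed correlations of 0.5 to 0.7 and a sustained effect. So 80% pairwise power is not shown; it is not ruled out under every pattern. That the reported calculation is omnibus does not depend on which route the sponsor took.

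**What to change.** In the Sample size section:
- name the effect-size metric, the G*Power test and any correlation actually used, from the sponsor's own record and not from the inference made here;
- state that the 80% refers to the omnibus interaction, if the record confirms it;
- do not let 0.20 stand as a small pairwise effect of EMI over EMA and control;
- add power or the detectable difference on the PHQ-9 for EMI versus EMA and for EMI versus wait-list, with the correlation and alpha stated. With 50 per arm at two-sided 0.05, this is about 0.57 SD unadjusted and 0.40 to 0.49 SD baseline-adjusted at correlations of 0.7 to 0.5;
- say that a non-significant EMI versus EMA result will be read through its confidence interval and not as proof of no added value.

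The cost is a few sentences and a less favourable power statement. No extra participants are needed, and by the article's own account recruitment had not started.

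### The 15% attrition allowance is applied the wrong way: 174 recruited leaves about 148 completers, not the 152 required, a minor shortfall that costs about one point of power

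*Protocol article*

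**What the plan says.** The Sample size section gives the inputs as "Assuming a conservative effect size of 0.20, an alpha level of 0.05, an 80% power", followed by "three groups, and 3 measurements, a sample of 152 was obtained". The next sentence is "Assuming a 15% of attrition, we will recruit a minimum of 174 participants". It does not write out the inflation formula, the test, the effect-size metric or a correlation between measurements.

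The total is repeated elsewhere. The Methods part of the Abstract says "the study sample will be composed of a minimum of 174 healthcare workers" and sets at least 58 in each of the three arms (3 x 58 = 174). Study aims and design again gives 174 as a minimum. Participants, recruitment, and eligibility criteria gives 174 as the sample, without calling it a minimum. The limitations paragraph of the Discussion says that dropout was allowed for in the sample size.

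On analysis, the Data analysis plan says "a multilevel linear mixed model, which effectively handles missing data, will be computed", with every assessment point in the model.

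**The concern.** An attrition allowance should ensure that, after the assumed loss, the number the power calculation needs is still there. Here it does not: taking 15% off the recruitment target gives fewer than 152. The likely cause is a common slip, adding 15% to the required number instead of dividing by the proportion expected to remain.

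What is at stake is whether the recruitment target, repeated in several sections, follows from the plan's own inputs. The 152 also carries no reserve: in the calculation that reproduces it, 152 is the smallest number that reaches 80%. Any shortfall therefore comes straight off the power.

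**Working it through.** **Inputs, all from the Sample size section:** effect size 0.20; alpha 0.05; power 80%; 3 groups; 3 measurements; required N = 152; attrition d = 15%; recruitment target 174.

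**Step 1. Reproduce 152.** Read the effect size as Cohen's f and the test as the group-by-time interaction in a repeated-measures analysis. With k = 3 groups and m = 3 measurements:

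- noncentrality = N x (m - 1) x f² = 152 x 2 x 0.04 = 12.16
- degrees of freedom = (m - 1)(k - 1) = 4 and (N - k)(m - 1) = 149 x 2 = 298
- power = 80.1%

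The smallest N that reaches 80% under this reading is exactly 152, so the figure is reproduced. The reading is inferred from that match. With f = 0.20 and an assumed correlation of 0.5, other standard variants give about 53 (interaction) or 164 (between groups).

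**Step 2. Reproduce 174.**

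| Method | Formula | Result |
|---|---|---|
| Add the percentage | 152 x (1 + 0.15) | 174.8 |
| Divide by the proportion retained | 152 / (1 - 0.15) | 178.8, so 179 |

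The stated 174 matches the first line with the fraction dropped (rounding up would give 175), and 174 divides into 58 per arm. It does not match the second. For three equal arms the second line becomes 180, or 60 per arm.

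**Step 3. What 174 leaves.**

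- Completers at 15% loss: 174 x 0.85 = 147.9, about 148, which is 152 - 148 = 4 short.
- Largest loss that still leaves 152: 1 - 152/174 = 12.6%.
- For comparison: 179 x 0.85 = 152.2 and 180 x 0.85 = 153.

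**Step 4. Effect on power, counting completers only, under the Step 1 reading.**

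| Completers | Power |
|---|---|
| 152 | 80.1% |
| 148 | 78.9% |
| 147 (49 per arm) | 78.6% |

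The loss is 80.1 - 78.9 = 1.2 points at 148 and 80.1 - 78.6 = 1.5 points at 147.

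**Step 5. Does the size of the loss depend on the inferred test?** Suppose only that some F test with 2 or 4 numerator degrees of freedom gives exactly 80% at 152, and scale its noncentrality by 148/152. Power at 148 is then 78.7% to 78.9%. So if 152 is taken as the number giving 80%, the one-point loss does not hinge on the exact variant.

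**The case against.** The case on the other side accepts the arithmetic slip and disputes its weight. Most of that case stands.

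- **The shortfall is small.** Four completers is 4/152 = 2.6% of the required number, and about one point of power changes no judgement of the trial's adequacy. This stands.
- **148 is a pessimistic count.** The planned mixed model uses every assessment point, so someone measured at two months but lost at three months' follow-up still contributes. This stands, with a limit: a participant lost straight after baseline gives no post-baseline outcome, and the model does not turn adding 15% into the correct allowance.
- **174 is a minimum.** That is how most sections put it, but the minimum is the number presented as sufficient at 15% loss, and the eligibility section gives 174 without that qualifier. This does not remove the discrepancy.
- **The power percentages rest on an inferred test.** This stands and should be said openly. The attrition arithmetic in Steps 2 and 3 does not depend on it.

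A reader might also infer that the 15% has no valid basis, because the app is self-administered while the section cites interventions "such as blended interventions, tend to obtain lower dropout rates". The documents do not support that. Blended interventions are named only as an example within the wider class of technology-based mental health interventions, and the cited review is not at hand to show what it covers. Nor do the documents give any basis for a particular higher attrition rate, so power at much heavier losses is no part of this point. The article also describes a contact procedure for app users who stop responding for four days, intended to limit attrition.

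**Conclusion.** The point holds as a minor arithmetic error. The required number, the attrition rate and the recruitment target in the Sample size section cannot all be right together: 174 with 15% loss leaves about 148, and 174 protects 152 only up to 12.6% loss. That conclusion needs nothing beyond the section's own figures. That the target was reached by multiplying by 1.15 is inferred from the numerical match, because no formula is printed.

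The size of the consequence is about one point of power, roughly 79% against 80%. This assumes that exactly 174 are recruited, that exactly 15% are lost, that only completers count, and that the test is the one that reproduces 152. Partial data in the mixed model would bring the figure somewhat closer to 80%.

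A reader might infer that the trial is underpowered in any material sense. The figures do not show that.

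**What to change.** Correct the attrition sentence in the Sample size section in one of two ways:

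1. **Keep 174 (58 per arm)** and state that it covers attrition up to about 12.6% and gives about 79% power at 15% when only completers are counted.
2. **State 179, or 180 (60 per arm) for equal arms,** as the number that corresponds to 15% attrition.

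Naming the test and the effect-size metric in the same sentence would let a reader confirm the power figure.

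Under either option, bring the places that repeat 174 or 58 per arm into line: the Abstract (Methods), Study aims and design, and Participants, recruitment, and eligibility criteria.

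The first option costs one reworded sentence. The second adds 179 - 174 = 5 participants, or 180 - 174 = 6 with equal arms. The article states that recruitment had not started, so either was open at that stage.

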### Measures description

#### Primary and secondary outcomes

The sociodemographic information (see Supplementary file 1) will be gathered with an ad hoc questionnaire that evaluates sex, age, specific healthcare profession, marital status, if they share their home with a COVID-19 vulnerable person, where they work (type of health care center, such us hospital, primary care, nurse home, etc.), if they work directly with COVID-19 patients, and number of COVID-19 deaths in their region (this will be collected from external, official sources) [2].

The primary outcome is the Brief Patient Health Questionnaire Mood Scale (PHQ-9) for depression. Secondary outcomes include the Emotion Regulation Questionnaire (ERQ), the Difficulties in Emotion Regulation Questionnaire (DERS), the Brief Resilience Scale (BRS), and the Short Professional Quality of Life Scale (ProQOL Short). Primary and secondary outcomes will be obtained at baseline, post-intervention, and 3-month follow-up.

The PHQ-9 is a 9-item depression module from the full PHQ where the user indicates the severity of depression during the previous 2 weeks. The symptom is presented in a scale measuring the frequency from 0 to 3 (0= “not at all” to 3 =” nearly every day”). The PHQ-9 has demonstrated its validity as a brief measure of depression severity in clinical samples [71] and the general population [72]. The PHQ-9 score is divided into the following severity categories: 5–9 (mild depression), 10–14 (moderate depression), 15–19 (moderately severe depression), and 20 or greater (severe depression). The range for the PHQ-9 is 0-to-27. The Spanish version of the scale has demonstrated good psychometric properties [73].

The ERQ is a 10-item self-report measure that evaluates the use of cognitive reappraisal and emotion suppression as ER efforts to regulate emotions [74, 75]. The items are rated on a 7-point scale (1 = “strongly disagree” to 7 = “strongly agree”). We will use the Spanish adaptation of the ERQ [76], which has obtained good internal reliability estimates for both reappraisal (.79) and suppression (.75).

The DERS [77] is a 28-item questionnaire that explores five dimensions of emotion dysregulation, including lack of control, life interference, lack of emotional attention, emotional confusion, and emotional rejection. Items are rated on a scale of 1 (“almost never”) to 5 (“almost always”). We used its Spanish adaptation [78]. The Cronbach’s alpha of the total dysregulation score has been excellent: .93 [77].

The BRS [79] evaluates resilience, understood as the ability to recover from stress. The BRS has 6 items rated from 1 (“strongly disagree”) to 5 (“strongly agree”). The scale has a Cronbach’s alpha of .80.

The ProQOL Short [80] is a 9-item questionnaire with 3 subscales: Compassion satisfaction, which evaluates the positive and altruistic aspects of the helping work, burnout, and secondary traumatic stress. The responses are rated on a 5-point Likert scale, in which participants indicate the frequency of each item in the last 30 days (1 = “never”, 2 = “rarely”, 3 = “Sometimes”, 4 = “Often”, and 5 = “Very Often”). ProQoL Short is based on version V of the Professional Quality of Life Scale. This questionnaire has been recently used in many studies about psychological effects of COVID-19 in healthcare professional [9, 81, 82] and its subscales have obtained good internal consistency estimates ranging from .75 to .88 [83]. ProQoL Short showed an adequate internal structure and invariance across the studied countries [80].

In addition to the clinical measures, we will evaluate typical outcomes in technology studies, namely usability and acceptability of the technology and fidelity with its use. Usability and acceptability of the technology will be measured with the Acceptability and System Usability Scale (SUS) and the Usability and Acceptability Questionnaire (CUA-Brief). The SUS [84] is a reliable, 10-item questionnaire that assess the usability of a technology application. The SUS has an acceptable reliability (Cronbach alpha of.91) [85]. Items are rated from 1 (“Strongly disagree”) to 5 (“Strongly agree”). Unacceptable usability could indicate that a user had difficulties while using the program, thus suggesting that the administration of the intervention through technological application could be considered a barrier for the clinical effect. The SUS can be interpreted with a qualitative scale (from “worst imaginable” to “best imaginable”) [86]. The CUA-Brief measures the acceptability of a technology using 7 items. It was designed ad hoc in a previous study. This is not an officially validated measure, but its Cronbach alpha in a previous study by our team was excellent: .94 [87]. The CUA-Brief allows to assess the user’s opinion about an application (perceived control while using the application, perceived ease-to-use of the app, intention to use the application in the future, confidence when using the app, feelings when using the app, and satisfaction with the size of the elements). All items are rated on a 5-point Likert scale ranging from 0 (“Totally disagree”) to 4 (“Totally agree”).

Finally, fidelity will be evaluated using passive outcomes, in line with past research. These measures will include the percentage of users making daily logins (at least 1) with respect to the total number of participants who started the treatment, the Percentage of users who continue to use the APP after 4 weeks, the Percentage of users who voluntarily use the APP outside the scheduled hours, and the Total time spent using the APP [88].

